### Randomization

Stratified permuted block randomization is used with stratification by gender and number of migraine days reported over the past 4 weeks (<8 days vs. ≥8 days). The block lengths are fixed and documented at the Institute of Medical Biometry and Statistics, University of Lübeck (IMBS), but are not available to those who enroll participants or assign interventions. MersenneTwister is used as a random number generator based on a real random seed from www.random.org. For the generation of the allocation sequence, RITA (version 1.50) is used.

A 1:1 randomization will be carried out. The randomization takes place centrally at the IMBS. At the beginning of the study, all future participants are randomized at once (list randomization). During the study, after enrolment of a single participant, a randomization form is filled in by the study center and sent (via fax or email) to the IMBS. This form includes the study ID, information on the strata, inclusion and exclusion criteria, name of the investigator, date and signature. At the IMBS, the validity of the enrolment is checked. If correct, the participant is registered in a data base, and the next allocation in the respective strata combination is selected. The allocation is noted on the randomization form, which is then signed and sent back to the study center.

Given the complex nature of the intervention, a blinding of the patients is not possible. The primary and secondary endpoints are based on patients’ assessment and therefore are not blinded.

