### Main study

After randomization, the main study comparing IV with CO begins. The use of the DTx represents the treatment in the IV phase after randomization. The DTx determines the personalized nutritional recommendation using data from a 10-day long CGM test phase followed by a 12-week nutritional intervention. The structure of the intervention phase is the same for all patients in IV, but the implemented nutritional recommendations are personalized.

A test kit and the use of one of the validated tissue glucose sensors (Dexcom G6 sensor and Abbott FreeStyle Libre sensors 1 and 2) are required for the IV. Immediately after randomization, the study site sends the test kits to the patient. After receiving the test kit, the individual test phase begins. For this purpose, the tissue glucose sensor is first applied according to the manufacturer’s instructions and remains there for at least 10 days. At the same time, food intake and other events such as sleep, everyday movement, and physical activity are recorded via the app. The state of health, stress, and migraine-specific symptoms are also logged via the app. The participants continue their usual eating habits and test the meals they like and eat frequently.

All data will be computed by Perfood GmbH in accordance with the sponsor’s internal SOPs, and the personalized nutrition recommendations are sent to the individual patients via their app. Immediately after receipt, consultations with nutrition experts are conducted voluntarily to ensure that the patient correctly understands all recommendations and are able to adjust his diet accordingly. Recommendations are also well explained in the app, ensuring understanding of the recommendations even if nutritional consulting is not realized. The intervention phase, in which the personalized nutritional recommendations are implemented, lasts 12 weeks until the endpoint is recorded. It thus represents the actual migraine prophylaxis by adhering to the personalized low-glycemic diet.

The CO is the non-application of the DTx while continuing the standard treatment. The study participants are provided with an app through which only the study-relevant questionnaires can be used. This ensures that there is no difference between the groups regarding the mode of assessment of the patient-reported outcomes. After the follow-up after 12 weeks and the individual end of the study, the DTx can be used.

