Adherence endpoints will be assessed to evaluate how strictly the patients adhered to the recommendations at the end of every week of intervention, totaling 12 time points. At each of these time points, the number of days a specific meal (breakfast, lunch, dinner, snack, beverage) was consumed is assessed as well as the number of days the recommendations for the specific meal were largely followed. From this, the total number of meals per week and the percentage of meals with followed recommendations are computed for every patient. From this, a patient will be defined to be non-adherent if the percentage of meals with followed recommendations is < 50%.

As safety endpoints, all adverse events (AEs) and serious adverse events (SAEs) as well as adverse device effects (ADEs) will be monitored.

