### Statistical analysis

For all analyses, all patients will be considered who were successfully randomized and gave their informed consent.

The primary endpoint and other efficacy endpoints will be evaluated in the full analysis (FA) set in which patients, in whom it becomes apparent after randomization that they have either (1) headaches other than migraine or tension-type, if the latter led to more than 50% of the headache days per month; or (2) 14 or more days with migraine headaches per month, are excluded. As a sensitivity analysis, all efficacy endpoints will be additionally evaluated in the intention to treat (ITT) and per protocol (PP) populations. Here, PP additionally excludes patients in whom the intervention was not started, who did not adhere to the recommendations as defined above, changed prophylactic treatment with change of the dose, a switch to another medication, or addition of another medication, or entered no data after the first 4 weeks of IV/CO. Safety endpoints will be evaluated in the safety analysis (SA) set that includes all randomized patients, but patients in IV in whom the intervention was not started or who did not adhere to the recommendations are analyzed as CO participants.

All variables at all time points and all defined primary, secondary and exploratory endpoints (i.e., changes from baseline to follow-up visits) will be described according to their type (measurement, normal, log-normal, ordinal, proportion) using standard metrics in all analysis sets. The disposition of patients will be described by a CONSORT flow chart.

For the primary objective regarding the primary efficacy endpoint, the primary hypothesis will be tested using a linear model in the FA analysis set. With *y*_*i*_ denoting the endpoint “change in the number of days with migraine symptoms at 12 weeks” in patient *i*, the linear model is defined as follows:$${y}_i={\beta}_0+{\beta}_1{x}_i^{\textrm{Treat}}+{\beta}_2{x}_i^{\textrm{Sex}}+{\beta}_3{x}_i^{\textrm{Baseline}}+{\varepsilon}_i,$$where

$${x}_i^{\textrm{Treat}}=\left\{\begin{array}{cc}\ 0,&\ \textrm{if}\ \textrm{CO},\\ {}\ 1,& \textrm{if}\ \textrm{IV}\end{array}\right.$$, $${x}_i^{\textrm{Sex}}=\left\{\begin{array}{cc}\ 0,&\ \textrm{if}\ \textrm{male},\\ {}\ 1,& \textrm{if}\ \textrm{female}\end{array}\right.$$, and $${x}_i^{\textrm{Baseline}}$$ is given by the number of days with migraine symptoms at baseline.

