### Missing data

#### The endpoints

Number of days with migraine headaches in the past 4 weeks,Number of days with acute migraine-specific medication in the past 4 weeks,Number of days with non-migraine headaches of moderate or severe intensity in the past 4 weeks,Number of migraine attacks in the past 4 weeks,Number of days without headaches in the past 4 weeks,Cumulative length in hours of migraine in the past 4 weeks, andCumulative length in hours of non-migraine headaches in the past 4 weeks

are based on counting the number of days, attacks, or hours, respectively, from the headache eDiary. The respective endpoints will be set to missing if patients made entries for less than 80% of the days, i.e., for less than 22 out of 28 days. If patients made entries for at least 80% but less than 100% of the days, the missing number of days, attacks, or hours will be imputed by the average of the valid entries.

The primary efficacy endpoint of this study is based on the number of days with migraine symptoms in the past 4 weeks at 12 weeks after intervention in IV or after randomization in CO (FU12). At FU12, missing values might occur for several reasons. Generally, we assume that patients in CO are likely to stop diary entries for no specific reason. Missing values in IV might occur in the following scenarios:Patients in IV might stop the intervention and corresponding diary entries early because of no effect. Their missing values should therefore be comparable to the values in CO, and this scenario hence assumes that values are missing not at random (MNAR).Patients in IV might stop the intervention and corresponding diary entries early for other reasons not related to the outcome. Alternatively, patients in IV might only stop diary entries but keep the same level of adherence. Thus, missing values should be comparable to the observed values in IV, and this scenario assumes that values are missing at random (MAR) or missing completely at random (MCAR).

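### The safety set counts non-adherent intervention patients as controls although they have normally worn the sensor and used the DTx; low adherence is not non-exposure

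*Protocol article*

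**What the plan says.** The Statistical analysis section of the protocol article puts all randomized patients in the safety analysis set, with one reallocation: "patients in IV in whom the intervention was not started or who did not adhere to the recommendations are analyzed as CO participants". There are two separate triggers, not starting and not adhering.

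The second trigger is defined under Endpoints: "a patient will be defined to be non-adherent if the percentage of meals with followed recommendations is < 50" per cent. The data come from questions asked "at the end of every week of intervention, totaling 12 time points". The same section states the safety endpoints: "all adverse events (AEs) and serious adverse events (SAEs) as well as adverse device effects (ADEs) will be monitored".

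On exposure, the Main study section says that in IV "the tissue glucose sensor is first applied according to the manufacturer’s instructions and remains there for at least 10 days". The recommendations are then computed from those data and the 12-week nutritional phase follows. For the other arm it says: "The CO is the non-application of the DTx while continuing the standard treatment". Control patients receive an app that offers only the study questionnaires.

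**The concern.** Moving patients who never started resembles the usual as-treated safety set and is not the difficulty. The difficulty is the second trigger. A patient who followed, say, 40% of the meal recommendations has used the sensor, the app and part of the diet, but is analysed in an arm defined by not having the DTx.

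The timing adds to this. Events during sensor wear come before any recommendation exists, yet the patient's later eating behaviour decides which arm they are charged to. A sensor-related adverse device effect could then be listed under controls, none of whom was given a sensor under the protocol.

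The classification is also made after randomization, on behaviour that an adverse event might change. At stake is the between-arm safety description. According to the Discussion, the clinical data go to the federal regulator for assessment.

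**Working it through.** **Figure in the plan.** The safety rule carries no figure. The only design number used here is 256 per group. It reproduces: the assumed difference is 1.704 - 0.912 = 0.792 days with SD 3.19, two-sided alpha 0.05 and power 0.80. The normal approximation gives 255; the t-test gives 255.6, rounded up to 256. Allocation is 1:1 ("A 1:1 randomization will be carried out").

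**Assumptions (not in the article).** True adverse event rate 20% in all IV patients and 10% in CO; 25% of IV non-adherent; non-adherers' event rate r left free. All IV patients are taken as exposed.

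**Set-up.** Moved patients: 0.25 × 256 = 64. Remaining IV: 192. Enlarged CO: 256 + 64 = 320. True events: IV 0.20 × 256 = 51.2; CO 0.10 × 256 = 25.6.

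- Reported IV rate = (51.2 - 64r)/192
- Reported CO rate = (25.6 + 64r)/320
- Reported difference = (0.2667 - 0.3333r) - (0.08 + 0.2r) = 0.1867 - 0.5333r

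| r | Reported IV | Reported CO | Reported difference (true: +10.0 points) |
|---|---|---|---|
| 10% | 44.8/192 = 23.3% | 32.0/320 = 10.0% | +13.3 |
| 20% | 38.4/192 = 20.0% | 38.4/320 = 12.0% | +8.0 |
| 35% | 28.8/192 = 15.0% | 48.0/320 = 15.0% | 0 |
| 40% | 25.6/192 = 13.3% | 51.2/320 = 16.0% | -2.7 |

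**Turning points.** The reported difference equals the true one where 0.1867 - 0.5333r = 0.10, so r is about 16%. Below that the rule inflates the difference; above it the rule attenuates it. The sign reverses only above r = 0.1867/0.5333 = 35%. At that point the adherers' rate is 15%, so non-adherers have about 2.3 times the adherers' risk.

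**Other assumed rates.** Let a be the adherers' risk, c the control risk and q the non-adherent share. By exposure the difference is (1 - q)a + qr - c. Under the rule it is a - (c + qr)/(1 + q). For q from 10% to 40%:

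- a = r = 15%, c = 5%: 10.0 points by exposure; 9.1 down to 7.1 under the rule.
- a = 15%, r = 30%, c = 5%: 11.5 up to 16.0 by exposure; 7.7 down to 2.9 under the rule.
- a = 5%, r = 20%, c = 2%: 4.5 up to 9.0 by exposure; +1.4 down to -2.1 under the rule.

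**Sensor-related events.** If the true control risk is zero, any such event in a moved patient produces a spurious control rate. With a = r = 5% and q = 20%, about 2.6 of 12.8 IV events move, and CO shows 0.8% instead of 0.

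**The case against.** The strongest reply is that the bias has no fixed direction. A reader might infer that the rule always understates harm in IV and overstates it in CO, or that the comparison will come out reversed. The article supports neither. Less exposure may mean fewer diet-related events, and with a low enough rate among non-adherers the rule exaggerates IV harm. Reversal needs a markedly higher risk among non-adherers. This part of the reply stands.

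A reader might also infer that patients who cut back because of an adverse event necessarily land below 50%. That is plausible but not stated. The missing-data section names lack of effect as one reason for stopping, and otherwise says only: "Patients in IV might stop the intervention and corresponding diary entries early for other reasons not related to the outcome". It does not mention adverse events. Nor does the article say how the weekly percentages are combined into one classification, so a late stopper could stay above the threshold. This also stands.

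Three further points carry some weight:

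- All events are still captured; only their tabulation by arm changes.
- No formal safety hypothesis is stated, and the gate-keeping concerns efficacy alone.
- The Statistical analysis section promises a description of all variables in all analysis sets, which could be read as including an as-randomized safety table. But that sentence does not name the safety endpoints, and the section assigns those specifically to the safety set.

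Controls are not app-free either: the Discussion describes their app as a modified version of the intervention. It provides questionnaires only, so they still have no sensor and no nutrition programme.

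None of this removes the core point, which follows from the article's own definitions: the rule places exposed patients in the unexposed arm.

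**Conclusion.** The point holds in this form: the non-adherence condition treats low adherence as if it were non-exposure. As a result, events under sensor or DTx use can be reported in an arm that has neither the sensor nor the nutrition programme. This needs no outside assumption.

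The numerical effect does. Under the main set of assumed rates, a true +10 points is reported as anything from +13.3 to -2.7 as non-adherers' event rate goes from 10% to 40%. These figures illustrate sensitivity and are not a forecast.

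How many patients would move is also unknown. The Discussion notes that app studies often see high discontinuation, but also that only regular app users from the baseline phase are randomized.

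The primary and secondary efficacy analyses, the type I error control and the sample size are not touched. Because the rule is stated outright in the article, it is an error to correct and not a detail left to the analysis plan.

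**What to change.** In the safety set definition, delete the second of the two reallocation conditions (non-adherence). State instead that every IV patient with any sensor application or any use of the DTx intervention is analysed as IV for safety, and that only IV patients with no such exposure are analysed with CO. Completing questionnaires in the app, which both arms do, should not count as exposure. Naming sensor application explicitly also settles whether a patient who wore the sensor but never reached the nutritional phase has started, which the article leaves open. Present adherence as a descriptive subgroup within IV.

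The cost is one sentence in the protocol, carried into the analysis plan. No extra patients or data are needed. The IV adverse event rate may look less favourable than under the present rule.

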### Sample size

The sample size was calculated with the aim to show a difference in the change in the number of days with migraine symptoms in the past 4 weeks at follow-up 12 compared with baseline.

To estimate the possible effect in the control group, eight studies were identified in which migraine patients in a control group received standard care or were placed in a waiting group [24–31]. These control patients were all aware of being in a control group, which is comparable to the planned study situation. Mean changes in migraine days with corresponding standard deviations and sample sizes were extracted from these publications and meta-analyzed using a random effects model. This yielded a pooled estimate of the mean change of 1.14 days.

The sample size was then calculated based on the following assumptions:Patients in the control group will experience a reduction similar to the reduction observed in the control groups in the literature, which was a reduction by 1.14 days on average.Patients in the intervention group will experience a reduction of at least 50% on average, which is recommended to be the minimally relevant effect [21]. Assuming that, at baseline, they will report a mean of 4.26 days as in our pre-study (internal data), this reduction corresponds to a mean change by 2.13 days.The drop-out rate is conservatively estimated to be 20% in every group. Although for the analysis of the primary endpoint, missing values will be imputed by multiple imputation, we assume a reduction of 0 days in patients with missing data for a conservative estimation of the sample size.In the intervention group, the average change is therefore estimated to be (0 days) × 20% + (2.13 days) × 80% = 1.704 days. In the control group, the average effect is therefore estimated to be (0 days) × 20% + (1.14 days) × 80% = 0.912 days.Based on values in the pre-study, the standard deviation of the change is set to 3.19 days.Significance level and power are set to α=0.05 (two-sided) and 1-β=0.8.To detect this effect using a two-group *t*-test requires that 256 patients per group are randomized (nQuery 4.0) [32].

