We test the hypotheses H0: *β*_1_ = 0 vs. H1: *β*_1_ ≠ 0with a linear model assuming variance homogeneity using a two-sided Wald test at significance level *α* = 0.05. The corresponding 95% Wald confidence interval will be estimated.

A sequential testing procedure will be used to maintain a family-wise type I error of 0.05 for primary and secondary endpoints. If the primary endpoint is statistically significant at *α* = 0.05, the secondary efficacy endpoints will be tested. Hence, positive results on secondary endpoints can be interpreted inferentially only if a treatment effect is shown on the primary endpoint (gate-keeping).

As a further gate-keeping test, the first secondary endpoint (change in the number of days with migraine symptoms at follow-up 12 compared with baseline after exclusion of non-adhering patients in IV) is tested first at *α* = 0.05. If this is significant, the other five secondary endpoints will be tested with significance levels adjusted according to Bonferroni-Holm [42]. If any null hypothesis is rejected, a difference between IV and CO in the respective endpoint is shown. If the null hypothesis is not rejected, it will not have been shown that there is a difference.

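### The first secondary test compares adherent intervention patients with all controls, which is not a randomized comparison, yet it is confirmatory and controls access to the other five secondary endpoints

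*Protocol article*

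**What the plan says.** The protocol article defines the first secondary endpoint (Study objectives and hypotheses; Endpoints) as the change in migraine days at follow-up 12, comparing adherent IV patients with CO. Adherence comes from weekly self-reports during the intervention: "a patient will be defined to be non-adherent if the percentage of meals with followed recommendations is < 50"%. CO receives no recommendations (Main study), so no corresponding exclusion exists there.

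Under Statistical analysis the primary is tested first. Next comes the change "compared with baseline after exclusion of non-adhering patients in IV) is tested first at" 0.05, described as a further gate-keeping step. Then: "If this is significant, the other five secondary endpoints will be tested with significance levels adjusted according to Bonferroni-Holm". The section adds that any rejected null hypothesis demonstrates a difference between IV and CO for that endpoint.

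The same section removes non-adherent patients from the per-protocol set, but uses that set only for sensitivity analysis.

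**The concern.** IV patients are dropped for behaviour that occurs after randomization, while CO keeps the patients who would have behaved the same way. If patients who follow the diet are also those who tend to improve, the two groups differ even when the product does nothing.

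The protocol itself makes such a link plausible. Its Missing data section supposes that IV patients may stop because they see no effect, and the primary analysis is built to guard against that. The first secondary test instead removes IV patients who stop following the diet.

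Two things are at stake. A selected contrast would carry a confirmatory label in a submission meant to show superiority to the regulator (Discussion). And response, HIT-6, MIDAS, EQ-5D-5L and acute-medication days, none of which has a one-arm exclusion, can be claimed only if that contrast succeeds.

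**Working it through.** **Inputs from Sample size.** Mean changes are 2.13 days (IV) and 1.14 days (CO) before dilution for drop-out. "The drop-out rate is conservatively estimated to be 20% in every group". "the standard deviation of the change is set to 3.19 days". "Significance level and power are set to α=0.05 (two-sided) and 1-β=0.8". The stated size is 256 per group.

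**Reproducing the plan's figure.** Planned difference = 0.8 × 2.13 − 0.8 × 1.14 = 1.704 − 0.912 = 0.792 days. n = 2 × (1.960 + 0.842)² × 3.19² / 0.792² gives 255 per group by the normal approximation. The exact t-test gives 256, with power 0.8006. The sample size is correct.

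**Assumptions.** The documents give neither the adherent fraction f nor the correlation r between the tendency to adhere and a patient's own improvement. I used f = 0.8, 0.7 and 0.5 and r = 0.1, 0.2 and 0.3 in a normal selection model. Secondary analyses use complete cases, so I took 256 × 0.8 = 204.8 completers per arm. This is a t-test approximation without the planned covariates.

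**Selection bias and stand-alone rejection rate with zero true effect.**
- λ = φ(z)/f, where z cuts off the upper fraction f: 0.350, 0.497 and 0.798 for f = 0.8, 0.7 and 0.5.
- Bias b = r × λ × 3.19.
- SE = 3.19 × √(1/(204.8 f) + 1/204.8): 0.334, 0.347 and 0.386.
- Rejection = Φ(b/SE − 1.96) + Φ(−b/SE − 1.96).

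Example, f = 0.7 and r = 0.2: b = 0.2 × 0.497 × 3.19 = 0.317 days; b/SE = 0.912; rejection 14.9%. The bias is 0.317/0.792 = 40% of the planned difference.

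| Adherent | r = 0.1 | r = 0.2 | r = 0.3 |
|---|---|---|---|
| 80% | 0.11 d, 6% | 0.22 d, 10% | 0.33 d, 17% |
| 70% | 0.16 d, 7% | 0.32 d, 15% | 0.47 d, 28% |
| 50% | 0.25 d, 10% | 0.51 d, 26% | 0.76 d, 51% |

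Allowing for the slightly smaller variance among selected patients moves these rates by less than two percentage points.

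**The procedure as planned, global null.** A claim on this endpoint needs the primary to be significant too, so the probability of passing both cannot exceed the primary's 5%. Simulations with 205 or 256 patients per arm, and a complete-data comparison standing in for the primary, gave about 2% to 4%.

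**Chance that the second step blocks the rest after a positive primary, no selection (r = 0).** Take a completer effect of 2.13 − 1.14 = 0.99 days and let the full completer comparison stand in for the primary: SE = 3.19 × √(2/204.8) = 0.315, power 88.1%. The two test statistics are correlated as 0.315/SE, so the joint probability follows from the bivariate normal.

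| Adherent | Second step alone | Both significant | Second step fails given primary |
|---|---|---|---|
| 80% | 84% | 82.8% | 6% |
| 70% | 81% | 79.8% | 9% |
| 50% | 73% | 71.2% | 19% |
| 40% | 66% | 64.6% | 27% |

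With 256 per arm and the 0.792-day effect instead, failure given a positive primary is about 8%, 12% and 24% at 80%, 70% and 50% adherent.

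**The same with r = 0.2.** Given a significant primary, the second step passes in more than 99% of simulated trials at every one of these adherence levels. It passes because selection adds to the effect.

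**The case against.** The strongest reply is that the primary protects the sequence, and this stands. A reader might take 15% or 26% as the trial's false-positive rate, but those figures describe the second test in isolation. If the primary effect is real, no benefit among adherers would require benefit confined to non-adherers, which is implausible for a diet programme. The realistic harm is an exaggerated or misread estimate, not a claim arising from nothing.

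A reader might also infer that bias will block the remaining endpoints. In the direction that is plausible here, with improving patients staying adherent, bias helps the test pass. Blocking arises mainly without selection, and its cost should be stated conditional on a positive primary (6% to 27%), not as unconditional power of 84% to 66%. If benefit acts through adherence, the effect in adherers is larger and blocking is rarer still.

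The five later endpoints are not beyond criticism: they share the full-analysis set's exclusions after randomization and the complete-case rule. Complete-case analysis therefore does not set this test apart. The one-arm behavioural exclusion does.

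Finally, f and r are assumed, and at 80% adherent with r = 0.1 the stand-alone rate is only 6%. That limits any statement about size. It does not restore a randomized comparison, and nothing elsewhere in the protocol does so.

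**Conclusion.** The point holds as a defect of hierarchy and interpretation. A non-randomized contrast has been given confirmatory status, and five endpoints without that defect depend on it. The possible selection bias runs from 0.11 to 0.76 days over the assumed ranges, so at the upper end it is nearly as large as the planned 0.792-day difference. With no selection, the step costs the other five endpoints their confirmatory status in roughly 6% to 27% of trials with a positive primary. With a correlation of 0.2 it almost always passes, for the wrong reason. As a gatekeeper it serves poorly in either case.

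The structural conclusion needs no assumption; the sizes rest on the assumed adherence fraction and correlation. The primary test, the sample size and error control under the global null are unaffected. This should be fixed, but it does not undermine the trial's main result.

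**What to change.** Take the adherent-subset endpoint out of the confirmatory sequence. Test the primary at two-sided 0.05; if it is significant, test the other five secondary endpoints with Bonferroni-Holm, the first step at 0.05/5 = 0.01. Report the adherent IV versus CO contrast as supportive and state that it is not a comparison of randomized groups. This matches the sensitivity role that the protocol already gives the per-protocol set, which uses the same exclusion.

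I would not substitute a complier-average estimate using randomization as the instrument. It needs no effect of assignment among non-adherers, which is hard to defend when patients know their allocation and those below the 50% cut-off may still follow some recommendations.

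The change is one of wording in the protocol and analysis plan, to be made before database lock. Family-wise error stays at 0.05 and the sample size at 256 per group. The sponsor gives up one confirmatory claim.
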